### Sample Size

A total of 30 patients, for whom all samples required for the study have been collected, should be included, distributed as follows:

Group 1: 15 patients with localized disease, for whom the 4 samples required for the study were collected.Group 2: 15 patients with metastatic disease, for whom the 3 samples required for the study were collected.

These numbers will provide preliminary data before considering a larger study. The primary objective of this study is to measure the markers of interest in patients. Given that the study focuses on rare cancers and that statistical analyses are only secondary objectives, no statistical power calculation has been performed for this study. Patients for whom the total number of required samples was not achieved will be replaced.

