### Statistical Analysis

Plasma exosomes as well as exosomal protein and RNA concentrations will be described by their mean (SD) and their median (with extent). Comparison of baseline concentrations of participants with localized disease versus metastatic disease will be performed using nonparametric Wilcoxon tests. Comparison of pretreatment and posttreatment (surgical or drug) concentrations will be performed using nonparametric tests for matched data. Analyses will be carried out by subgroup (metastatic and localized) and on the whole population. Relative exosome variation before and after treatment will be compared in responders and nonresponders using nonparametric Wilcoxon tests. A Bonferroni correction will be applied to the *P* value to adjust the significance threshold during multiple comparisons.

The area under the receiver operating characteristic curve (AUC) modeling the response to treatment in function of initial exosome concentration will be plotted. AUCs with 95% CI values will be provided. The model will be adjusted to the type of disease (localized or metastatic). An exosome concentration threshold, predictive of response to treatment, will be determined. Performance (ie, sensitivity, specificity, and predictive values) associated with this threshold will be calculated. A similar approach will be followed concerning exosome concentration after treatment and delta between initial and posttreatment values. Different protein and RNA-derived markers will be analyzed. Performance associated to the absence or presence of these markers to predict response to treatment will be determined for each of the markers. Analyses will be performed under the software SAS 9.4 (SAS Institute).

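### The response AUC from a model adjusted for disease type measures exosomes plus disease type, so neither it nor the pooled threshold figures should be read as exosome performance

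*Protocol article*

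**What the plan says.** All of the following stands in the protocol article.

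- **Statistical Analysis, second paragraph.** The AUC is for a curve "modeling the response to treatment in function of initial exosome concentration will be plotted", with a 95% CI. Then: "The model will be adjusted to the type of disease (localized or metastatic").
- **Same paragraph, threshold.** "An exosome concentration threshold, predictive of response to treatment, will be determined". No threshold per disease type is mentioned. On how the cut-off performs, the section adds: "Performance (ie, sensitivity, specificity, and predictive values) associated with this threshold will be calculated".
- **Same paragraph, repetition.** "A similar approach will be followed concerning exosome concentration after treatment and delta between initial and posttreatment values". One specification therefore drives three sets of results.
- **Statistical Analysis, first paragraph**, among the Wilcoxon and matched-data comparisons: "Analyses will be carried out by subgroup (metastatic and localized) and on the whole population".
- **Sample Size.** The localized cohort is set as "Group 1: 15 patients with localized disease, for whom the 4 samples required for the study were collected", and the metastatic cohort is likewise set as "Group 2: 15 patients with metastatic disease, for whom the 3 samples required for the study were collected". The section says that no power calculation was made and that statistical analyses are secondary.
- **Study Objectives and Endpoints.** The treatment around which samples are taken is surgery in localized disease and first-line chemotherapy in metastatic disease.
- **Results.** Exosome concentration and content are expected to differ by stage.

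**The concern.** Three results are at risk of being credited to exosomes when they partly reflect stage.

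1. **The AUC.** With disease type in the model, the fitted score ranks patients by exosomes and by cohort. Every comparison of a responder in one cohort with a nonresponder in the other is helped by the cohort term. The reference value for a useless marker is then the AUC of disease type alone, not 0.5. The two cohorts are treated differently, so equal response rates cannot be presumed.
2. **The threshold.** In an additive model, one cut-off on predicted probability corresponds to two exosome concentrations, one per disease type. A cut-off taken from the pooled, unadjusted curve avoids that, but may be confounded by stage, because the article itself expects concentrations to differ by stage.
3. **The predictive values.** PPV and NPV on the pooled sample depend on the pooled response rate. That rate is partly set by the 15:15 quota, a design choice and not a prevalence.

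Association with response is a stated secondary objective, and the Discussion says that positive results would lead to a nationwide study. A stage effect reported as a marker effect could be carried into that study.

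**Working it through.** **Inputs.** From the article: 15 localized and 15 metastatic patients, and a model with exosome concentration and disease type. The article states no AUC, response rate or threshold value, so there is no figure to reproduce. The response rates pL (localized) and pM (metastatic) below are assumptions. Swapping which cohort has the higher rate does not change the AUC of disease type alone once it is oriented to the better-responding cohort.

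**Step 1: AUC of disease type alone, equal cohorts.**

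AUC = 0.5 + 0.5 × [pL/(pL+pM) − (1−pL)/(2−pL−pM)]

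- 40/20: 0.5 + 0.5 × (0.4/0.6 − 0.6/1.4) = 0.5 + 0.5 × (0.667 − 0.429) = 0.62
- 50/20: 0.5 + 0.5 × (0.5/0.7 − 0.5/1.3) = 0.5 + 0.5 × (0.7143 − 0.3846) = 0.6648, or 0.66
- 80/20: 0.5 + 0.5 × (0.8 − 0.2) = 0.80

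**Step 2: the adjusted model with a useless marker.** About 4,000 simulated trials per setting, 15+15 patients, with the marker independent of response within each cohort. A logistic model of response on marker and disease type was fitted, and its AUC was taken on the same 30 patients. The last column is the marker's AUC using only pairs of patients with the same disease type.

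| Assumed rates (%) | Disease type alone | Adjusted model, mean in-sample AUC | Within disease type, mean |
|---|---|---|---|
| 50/50 | 0.50 | 0.63 | 0.50 |
| 40/20 | 0.62 | 0.69 | 0.50 |
| 50/20 | 0.66 | 0.72 | 0.50 |
| 60/40 | 0.60 | 0.67 | 0.50 |
| 70/30 | 0.70 | 0.75 | 0.50 |
| 80/20 | 0.80 | 0.84 | 0.50 |

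The chance that the model AUC reaches 0.70 with a useless marker was 18% at 50/50, 33% at 60/40, 72% at 70/30 and 96% at 80/20.

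**Step 3: separating the two sources.** At equal rates stage contributes nothing, yet the model AUC averages 0.63. That excess of 0.63 − 0.50 = 0.13 is small-sample optimism from fitting and evaluating on the same 30 patients. At 80/20, stage accounts for 0.80 − 0.50 = 0.30 and the remainder is 0.84 − 0.80 = 0.04. The mix depends on the rates.

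**Step 4: threshold.** For logit(p) = a + b·x + c·g, with x in SD units and g the disease type, one probability cut-off gives two concentrations |c/b| apart. Taking c as the difference in logits of the assumed rates:

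- 70/30, slope −1 per SD: |c| = 2 × ln(0.7/0.3) = 1.69, so the gap is 1.69 SD.
- 80/20, slope −0.5 per SD: |c| = 2 × ln(0.8/0.2) = 2.77, so the gap is 2.77/0.5 = 5.5 SD.

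If the cut-off is read from the pooled unadjusted curve, suppose that concentrations are 1 SD higher in the cohort that responds less and that the marker carries no information within cohort. The pooled marker AUC then averages 0.61 at 70/30 and 0.66 at 80/20.

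**Step 5: predictive values.** With sensitivity and specificity both held at 0.70 in each cohort (an assumption), PPV = 0.7p/(0.7p + 0.3(1−p)).

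- p = 0.2: 0.14/(0.14 + 0.24) = 0.37
- p = 0.3: 0.21/(0.21 + 0.21) = 0.50
- p = 0.5: 0.35/(0.35 + 0.15) = 0.70
- p = 0.8: 0.56/(0.56 + 0.06) = 0.90

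At 80/20 the pooled rate is 50%, so the pooled PPV of 0.70 describes neither cohort (0.90 and 0.37). At 40/20 the pooled rate is 30% and the contrast is milder: 0.50 pooled against 0.37 in the lower cohort.

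**The case against.** **The wording may mean something else.** The curve is described as a function of exosome concentration, AUCs appear in the plural, and adjustment could mean a stratified or covariate-adjusted ROC. The sentence on subgroup analyses carries no explicit limit to the rank tests. If either covers the ROC, the problem is largely removed. This stands as a reason to ask for clarification. It does not dispose of the point: a model described as adjusted for a variable reads most plainly as having it as a covariate. Disease type is constant within a subgroup, so that model can only be fitted on the whole population. Subgroup ROCs, if added, would leave the pooled adjusted AUC in place.

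**A reader might infer that the AUC is bound to be inflated by stage.** The document does not support that. It gives no response rate for either cohort, and its Results section expects exosome profiles, not response rates, to differ. At equal rates only optimism remains.

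**A reader might infer that the threshold and predictive values are meaningless.** That goes too far. A pooled cut-off on the concentration scale can be calculated and described. It only cannot be taken as the performance of exosomes.

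**A reader might infer that the pilot's go-ahead hangs on this AUC.** The Discussion speaks only of positive results and names no AUC criterion, and the Sample Size section makes statistical analyses secondary.

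**The remedy has limits.** At 20% response, a cohort of 15 has 15 × 0.2 = 3 responders, so a threshold from that cohort would be very unstable. This stands, and it is why per-cohort thresholds can only be exploratory.

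**Conclusion.** The point holds, with limits. On the plain reading, the planned AUC combines exosomes and disease type. Its no-information value is above 0.5 whenever the cohorts' response rates differ: 0.62 at 40/20, 0.66 at 50/20 and 0.80 at 80/20. In-sample means with a useless marker are about 0.69, 0.72 and 0.84, and these include optimism that would be present, at 0.63, with no stage effect at all. The threshold is either not unique (covariate model) or possibly confounded by stage (pooled curve), and pooled predictive values depend on the quota.

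The size rests on assumed response rates, a logistic model with additive terms, and AUCs evaluated on the data used for fitting. The point is of moderate weight: it concerns a secondary, exploratory analysis whose results may shape the nationwide study. The descriptive primary objective is unaffected.

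**What to change.** 1. State what adjustment for disease type means in the ROC analysis.
2. Make the reported exosome AUC the one computed within disease type: per cohort, or as a single stratified (covariate-adjusted) AUC that compares responders with nonresponders of the same disease type only.
3. If the covariate model is kept, print beside it the AUC of disease type alone and the increment from exosomes, with an optimism correction by resampling.
4. Give the threshold's sensitivity, specificity and predictive values by cohort, labelled exploratory, with the number of responders shown. Pooled predictive values may be tabulated but should not be presented as exosome performance.
5. Apply the same rules to the posttreatment concentration and to the change from baseline.

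**Cost.** A few sentences in the plan and a few lines of SAS, with no new patients or samples. The price is precision. For a useless marker, the stratified AUC ranges from about 0.27 to 0.72 (2.5th to 97.5th percentile) at 50/50 and from about 0.19 to 0.80 at 80/20. Thresholds will be unstable where responders are few. That width is what 15 patients per cohort can support.

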### Study Objectives and Endpoints

The main objective of this pilot study is to quantify exosomes from plasma and to analyze protein and RNA content in patients with sarcoma, with localized or metastatic disease. Analysis will be performed before and after surgery in localized disease and before and after first-line chemotherapy in metastatic sarcoma. Some patients may have received neoadjuvant chemotherapy with or without radiotherapy.

The secondary objectives are to:

Determine whether the initial exosome concentration, protein, and RNA profile vary in the plasma with localized or metastatic stage of the disease.Determine whether the exosome concentration as well as protein and RNA profile varies upon treatment.Determine whether the initial exosome concentration (T0) is associated with a response to treatment.Determine whether changes in exosome concentration before and after treatment are associated with a response to treatment.

The primary endpoint of the study is the quantification of exosome concentration in the blood, as well as the measurement of protein and RNA levels after exosome lysis. Measures will be performed before and after surgery in case of localized disease and before and after chemotherapy in case of metastatic disease.

The secondary endpoints will be exosome blood concentration, as well as protein and RNA concentrations measured after exosome lysis. Treatment response and tumor progression (locoregional or appearance of metastases) will be assessed by magnetic resonance imaging (MRI) or computed tomography (CT) scan using RECIST (Response Evaluation Criteria in Solid Tumors) V1.1 criteria.

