### Extracellular Vesicle Analysis

Thawed plasma samples will be processed to centrifugation at 2000 g at 4 °C for 20 minutes. Exosomes will be extracted with Total sEV Precipitation Reagent (4484450, Thermo Fisher Scientific) for 10 minutes following homogenization. Part of the EVs will be used to determine their concentration and distribution profile using Nanotracking Analysis (NS300, Malvern). The data will be analyzed using Nanosight NTA 3.2 Analytical Software (Malvern Instruments). The other part will be used for the analysis of EV contents (proteins and RNA) and stored at –80 °C. Content analysis (proteins and RNA) will be performed using Western blot analysis, enzyme-linked immunosorbent assay, and RNA sequencing (Illumina) approaches. It is expected that all collected blood will be used for extracellular vesicles and content analysis.

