### Data Collection

The following data will be collected during the study, at the time of inclusion, and during medical follow-up: demographic and clinical data (age, sex, weight, height, performance status, etc), medical history, date of diagnosis, first-line treatment, disease evaluation reports (biological, imaging, etc), exosome analysis data (total exosome concentration, HSP70 exosome concentration, and multiple miRNA dosing). These data will be sent as a standard report from the laboratory in charge of these analyses (Inserm UMR1231). All data will be recorded in a Case Report Form (CRF).

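### For response prediction, the stated marker analysis reduces protein and RNA levels to absent or present, losing about a third or more of the information in 30 patients

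*Protocol article*

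**What the plan says.** All places are in the protocol article, Methods.

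- **Study Objectives and Endpoints** defines the protein and RNA endpoints as quantities. The primary endpoint includes "the measurement of protein and RNA levels after exosome lysis", and the secondary endpoints include "protein and RNA concentrations measured after exosome lysis".
- **Extracellular Vesicle Analysis** gives the assays: "Content analysis (proteins and RNA) will be performed using Western blot analysis, enzyme-linked immunosorbent assay, and RNA sequencing (Illumina) approaches".
- **Data Collection** lists the laboratory data to be recorded as "total exosome concentration, HSP70 exosome concentration, and multiple miRNA dosing".
- **Statistical Analysis** summarises exosomal protein and RNA concentrations by mean and median, and compares concentrations by stage and before versus after treatment.
- For response, the same section plans an AUC "modeling the response to treatment in function of initial exosome concentration will be plotted", with a 95% confidence interval and then a threshold with its sensitivity, specificity and predictive values. It extends this approach to exosome concentration after treatment and to the change. The rank comparison of responders with nonresponders also names exosome variation only.
- For protein and RNA markers the stated response analysis is: "Performance associated to the absence or presence of these markers to predict response to treatment will be determined for each of the markers". The sentence before it says that various markers will be analysed but names no method.

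**The concern.** Two kinds of quantitative measurement are treated differently in one paragraph, and no reason is given. Exosome concentration keeps its scale when related to response. A marker measured by ELISA, miRNA dosing or sequencing is reduced to yes or no for the same question.

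If presence means detection by the assay, a marker found in nearly every patient can show almost no discrimination, however far its level separates responders from nonresponders. The stage and before/after comparisons keep the level, but they do not address response.

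The article presents the 30 patients as preliminary data ahead of a possible larger study. What it reports about each marker's link with response is therefore likely to influence what is carried forward.

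**Working it through.** **What can be reproduced.** The only planned figure is the sample size, 15 + 15 = 30. The article states that no power calculation was made and gives no response rate, marker effect or positivity rate. Everything below rests on assumptions, shown as ranges.

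**Step 1: information lost by a yes/no cut.** For a normally distributed marker and a small effect, the efficiency of the cut relative to the level is φ(c)² / [p(1 − p)]. Here p is the share of patients positive, c the matching normal cut point and φ the normal density.

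| Share positive | Efficiency | Loss | 30 patients worth about |
|---|---|---|---|
| 50% | 0.3989² / 0.25 = 0.637 | 36% | 19.1 |
| 80% (or 20%) | 0.2800² / 0.16 = 0.490 | 51% | 14.7 |
| 90% (or 10%) | 0.1755² / 0.09 = 0.342 | 66% | 10.3 |

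The loss equals one half at p = 0.209, so it exceeds one half only below about 21% or above about 79% positive.

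**Step 2: apparent discrimination, with no test involved.** Assume two unit-variance normal distributions with true AUC 0.80. Their means differ by √2 × 0.8416 = 1.190. The detection limit is set so that the stated share of all patients is positive. The AUC of the yes/no marker is 0.5 + 0.5 × the absolute difference in positivity between the groups.

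Example: 12 responders, 18 nonresponders, higher levels in responders, 80% positive overall. Positivity is 0.96 in responders and 0.70 in nonresponders, so the AUC is 0.5 + 0.5 × 0.26 = 0.63. Over splits 15:15, 12:18 and 10:20 and both directions, the AUC of 0.80 falls to about 0.72 (50% positive), 0.62 to 0.67 (80%) and 0.57 to 0.61 (90%).

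**Step 3: power at two-sided 5%, unadjusted, true AUC 0.80.** Level: Wilcoxon rank-sum test, 4,000 simulated data sets per row. Presence: Fisher's exact test, summing the two binomial probabilities over all tables with P < .05.

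| Responders : nonresponders | Level in responders | Level, all values measured | Presence, 50% positive | 80% | 90% |
|---|---|---|---|---|---|
| 15:15 | either | 85% | 55.1% | 35.9% | 9.5% |
| 12:18 | higher | 85% | 56.7% | 21.8% | 1.3% |
| 12:18 | lower | 84% | 56.7% | 48.7% | 18.7% |
| 10:20 | higher | 80% | 52.0% | 12.5% | 0.4% |
| 10:20 | lower | 81% | 52.0% | 53.4% | 32.3% |

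**Step 4: sensitivity.**

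- *Detection limit kept.* With undetected values tied at the lowest rank, power on the level is 69 to 80% when half of patients are above the limit, and 80 to 85% when 80% or 90% are.
- *Weaker marker, AUC 0.70, same splits.* Level 41 to 48%; Fisher 21 to 23%, 6 to 24% and under 1% to 15% at 50%, 80% and 90% positive.
- *Less conservative test, AUC 0.80.* An uncorrected chi-square gives 66 to 71%, 22 to 61% and 2 to 48%.
- *Very uneven split, 5:25, responders higher (3,000 runs).* At AUC 0.80 the level has 59%, against Fisher 31%, 45% and 29% at 50%, 25% and 10% positive. At AUC 0.70 the level has 26% and the uncorrected chi-square 23%, 27% and 26%, so the gap closes. Expected counts there are as low as 5 × 0.10 = 0.5, where that test is unreliable.

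**The case against.** **Size of the loss.** A reader might infer that most of the information is thrown away. The documents do not support that. They give no positivity rate, and at an even split the loss is about one third. The lowest powers in the table also depend on direction. The article's only hint on direction, under Results, is that high baseline exosome concentration may go with worse disease; it says nothing of individual markers. The ranges matter more than any single cell.

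**Power as the measure.** The article names no test for the markers, only performance, and treats statistical analyses as secondary. Part of the power gap is Fisher's conservatism. This stands, but Steps 1 and 2 use no test and show the loss anyway.

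**A condensed article.** The full protocol or a statistical analysis plan may add a level-based analysis, and the preceding sentence is open-ended. So the point is limited to what is stated. It is still not a complaint about missing detail: the article commits to a method, and that method is the weaker one for a measured level.

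**Assays and the meaning of presence.** Western blot is among the assays, the article does not say which marker is read by which assay, and presence could mean exceeding a threshold rather than detection. A band-only marker suits a yes/no reading. For a threshold, Step 1 still applies; the remark about nearly universal markers applies only if presence means detection.

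**Consequences.** A reader might infer that levels are lost to the study, or that a stated rule would drop useful markers. Neither is in the text. Levels are still measured, described and compared by stage and over treatment, and no marker-selection rule is given. The listed secondary objectives also tie response to exosome concentration, not to individual markers.

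**Conclusion.** The point holds for response prediction only. The stated marker analysis turns measured levels into absent or present, out of line with the handling of exosome concentration in the same paragraph.

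Under a normal-marker assumption the cost is at least about one third of the information, and more than half only for markers positive in fewer than about 21% or more than about 79% of patients. At a true AUC of 0.80 and splits between 15:15 and 10:20, the level outperforms presence/absence in every setting tried, with either test. The gap ranges from moderate to very large and can close for a weak marker with very few responders. Bonferroni correction would lower all the absolute powers.

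This does not touch the primary objective of measuring the markers. It is an avoidable weakness in a stated analysis, worth correcting because it is nearly free.

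**What to change.** In Statistical Analysis, replace the marker sentence with a rule to this effect:

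- For each protein or RNA marker with a measured level, report the AUC for response with its 95% confidence interval, in the form already planned for exosome concentration. Give values below the detection limit the lowest tied rank.
- Report presence/absence performance as secondary. Make it the main reading only for markers read solely as a Western blot band.
- Fix the detection limit, or other definition of presence, for each marker before response data are examined.

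The cost is a change of wording: the samples, assays and ROC code stay the same. The downside is somewhat more output and a less simple presentation than yes/no.

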## Introduction

Sarcomas are rare cancers representing 1%-2% of all adult cancers with more than 5000 cases per year in France recently [1]. They affect men and women of all ages and constitute a heterogeneous group of tumors, with more than 70 different histological types and subtypes [2]. Despite adapted therapies, the metastatic risk of these diseases currently has a major negative impact on patient survival. Metastatic dissemination of tumor cells is responsible in most cases for patient death. The estimation of sarcoma’s metastatic risk is complex, given the histological heterogeneity of this pathology. It is therefore essential that, at diagnosis, a reliable evaluation of metastatic potential may be determined to better adapt the therapeutic strategy. Currently, the estimation of this risk is based essentially on histological criteria, namely the tumor grade. In recent years, large-scale genome and transcriptome analyses have allowed the identification of tumor molecular signatures predictive of prognosis. However, results reproducibility can be discussed, and the biological and prognostic significance remains limited. It is therefore necessary to find new biomarkers.

It has recently been found that sarcoma tumor cells secrete extracellular vesicles (EVs) [3] including small EVs (sEVs). In this study protocol, we will use the term exosomes to refer to small EVs. Exosomes are nanovesicles secreted by all the cells of the human body and found in abundance in different biological fluids such as blood, urine, saliva, and breast milk. Recently, the role and involvement of exosomes in sarcoma [4,5] development have been demonstrated [6]. Indeed, exosomes seem to play an important role in tumorigenesis, growth, tumor progression, and metastases appearance. Exosomes contain many proteins and nucleic acids (DNA, RNA, and microRNA), reflecting tumor characteristics. It has been shown that the amount of exosomes can be correlated with the grade of tumor malignancy [7,8]. Present in the blood, they offer the possibility of a noninvasive analysis of cancer cell molecular information by liquid biopsy. Recent preclinical studies have demonstrated strong changes in more than 1200 transcripts present in exosomes derived from Ewing sarcoma cells. Therefore, the study of plasma-derived exosomes in patients with sarcoma has a high potential to evaluate cancer pathogenesis, progression, and treatment efficacy.

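### Marker-by-marker prediction of response is planned on an unbounded protein and RNA set in 30 patients; the Bonferroni rule covers P values only, so the best markers will look better than they are

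*Protocol article*

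**What the plan says.** All references are to the protocol article.

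- **Statistical Analysis**, second paragraph, leaves the marker set open: "Different protein and RNA-derived markers will be analyzed". The next sentence fixes the procedure: "Performance associated to the absence or presence of these markers to predict response to treatment will be determined for each of the markers". Just before, performance is defined, for the exosome threshold, as sensitivity, specificity and predictive values.
- **Extracellular Vesicle Analysis** gives the source of the markers: "Content analysis (proteins and RNA) will be performed using Western blot analysis, enzyme-linked immunosorbent assay, and RNA sequencing (Illumina) approaches". No number of RNA markers is given.
- **Data Collection** is narrower but not a closed list: "total exosome concentration, HSP70 exosome concentration, and multiple miRNA dosing". HSP70 is the only named protein, and the miRNAs are neither named nor counted.
- **Statistical Analysis**, first paragraph, has the only multiplicity rule. It follows the Wilcoxon and matched-data tests and applies Bonferroni to the P value "to adjust the significance threshold during multiple comparisons".
- **Sample Size**: "A total of 30 patients, for whom all samples required for the study have been collected, should be included", split into 15 localized and 15 metastatic.

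The ROC model for response covers both disease types, with adjustment for type. The first paragraph also provides for subgroup and whole-population analyses. Neither paragraph says which population the marker-by-marker performance will use.

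**The concern.** The step with potentially the most comparisons is the one that the multiplicity rule misses. Sensitivity, specificity and predictive values carry no P value as planned, so a correction of P values leaves them untouched. No resampling, validation or best-of-many reference is described for them. When many markers are evaluated in few patients, the largest observed performance is inflated by selection even if no marker is related to response. This differs from the optimism of an optimized cut-off: it arises with a fixed present/absent call and no threshold search.

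The Discussion makes a nationwide study conditional on positive pilot results. Marker performance is a natural basis for that decision, and uncorrected figures for the leading markers would overstate the case for them.

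**Working it through.** There is no planned figure to reproduce. The Sample Size section states that no power calculation was done, and no response rate or marker count is given.

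**Inputs from the article:** 30 patients, 15 per disease group; present/absent markers; performance measured by sensitivity and specificity.

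**Assumptions:** markers are independent of response and of each other; detection probability is uniform between 0.1 and 0.9; presence or absence may be the positive call; m = 10 to 1200 markers; 6 to 15 responders of 30, or 3 to 7 of 15. An 80%/80% marker has sensitivity and specificity both at least 80%.

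**Formulas.** Let p be the chance that one null marker reaches 80%/80% in either direction. The expected number is m × p, and the chance of at least one is 1 − (1 − p)^m. For the best marker, let G(y) be the probability that one null marker has |sensitivity + specificity − 1| at most y. The median best Youden index is the smallest y with G(y)^m ≥ 0.5.

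**One case by hand, detection probability 0.5:**

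- 15 patients, 5 responders. At least 4 of 5 responders positive: 6/32 = 0.1875. At most 2 of 10 non-responders positive: 56/1024 = 0.0547. Product 0.01025; two directions, p = 0.0205.
- 30 patients, 9 responders. At least 8 of 9 positive: 10/512 = 0.0195. At most 4 of 21 positive: 0.0036. Product 0.00007; two directions, p = 0.00014.

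**Averaged over detection probabilities 0.1 to 0.9 (exact enumeration):** p = 0.0116 for 5 of 15 and 0.00008 for 9 of 30.

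| Patients / responders | Markers | Median best Youden | Expected 80%/80% markers | Chance of at least one |
|---|---|---|---|---|
| 30 / 9 | 10 | about 0.32 | 0.001 | 0.1% |
| 30 / 9 | 20 | 0.38 | 0.002 | 0.2% |
| 30 / 9 | 100 | 0.49 | 0.008 | 0.8% |
| 30 / 9 | 1200 | 0.62 | 0.10 | 9% |
| 15 / 5 | 20 | 0.50 | 0.23 | 21% |
| 15 / 5 | 100 | 0.70 | 1.2 | 69% |
| 15 / 5 | 1200 | 0.80 | 14 | >99% |

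With 9 responders, a Youden index of 0.49 is, for example, 7/9 = 78% sensitivity with 15/21 = 71% specificity. An index of 0.62 is, for example, 6/9 = 67% with 20/21 = 95%.

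**Dependence on the responder count, 1200 markers:**

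- 15 patients: 6.1, 2.9, 14, 2.7 and 2.2 expected 80%/80% markers for 3, 4, 5, 6 and 7 responders. The value for 5 is high because 80% of 5 is exactly 4, whereas with 4 responders all 4 are needed.
- 30 patients: from 0.05 (14 responders) to 0.8 (6 responders, a 55% chance of at least one). The median best Youden index stays between about 0.58 and 0.71.

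**Would extending Bonferroni help?** Suppose each marker had a Fisher test at an overall 0.05. With 5 of 15 responders, the smallest attainable P value is 1/3003 = 0.00033. Since 0.05/0.00033 = 150, even a perfect marker could not pass among more than 150.

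**The case against.** Four points weigh against a strong reading.

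1. **Population.** A reader might infer that marker performance is assessed in 15 patients. The article does not say so. It plans 30, the response model in the same paragraph includes both disease types, and the subgroup sentence stands with the Wilcoxon and matched tests and also covers the whole population. Fifteen is a possible analysis size, not the stated one.
2. **Marker count.** The Introduction's "strong changes in more than 1200 transcripts present in exosomes derived from Ewing sarcoma cells" is preclinical background, and Ewing sarcoma is not among the three named histologies. It indicates scale at most and is not this trial's marker set. With 10 to 20 markers in 30 patients, the chance of a useless 80%/80% marker is about 1% or less. That some useless markers will look highly predictive is therefore not established.
3. **Documents not shown.** The full protocol and any SAP may hold a marker list. The article also says that performance will be determined for every marker; reporting all of them would limit selective reporting.
4. **Pilot purpose.** The study is meant to give preliminary data, statistical analyses are secondary, and a larger study would validate the findings. Some false leads are an ordinary cost of a pilot.

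Points 1 and 2 stand and limit the size of the problem. Point 3 stands only in part: a missing list alone would be no finding, but the article does state a multiplicity rule, and that rule does not cover this step. Reporting every marker also does not tell a reader how good the best of many is expected to look by chance. Point 4 lowers the stakes but does not justify uncorrected figures in the decision to go on.

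**Conclusion.** The point holds in limited form. Predictive performance is planned for each marker of an unbounded set that includes RNA sequencing output, and the stated correction does not act on the measures reported. The best markers' apparent performance will be optimistic.

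In the pooled 30 patients the effect is mainly an inflated leading figure: a Youden index of about 0.4 to 0.6 from markers with no value, for 20 to 1200 markers and 9 responders. Chance markers at 80%/80% are uncommon there, except with few responders and a very large set. In a single disease group of 15 they become likely with hundreds of markers or more.

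These sizes rest on assumed marker counts, responder counts, detection probabilities and independence. Correlated markers would act like a smaller number.

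**What to change.** In Statistical Analysis:

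1. Name the primary protein and miRNA markers before response data are linked to the assay results. HSP70 exosomes and the miRNAs to be dosed under Data Collection are natural candidates.
2. State the population used for marker performance: pooled, by disease group, or both.
3. Label all other sequencing-derived markers as discovery.
4. Report any best marker beside a max-statistic reference: permute the response labels within disease group, recompute the best performance over all markers each time, and show where the observed best falls in that distribution. This uses the actual marker count and correlations, so it needs none of the assumptions above about them.

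Labelling the results exploratory and giving confidence intervals is a lighter alternative, but ordinary intervals for single markers do not account for selecting the best.

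The cost is added analysis text and a permutation run, with no extra patients or samples. Fewer markers receive a formal performance figure, and the headline performance will look less favourable.
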